### Intended statistical analyses

The primary objective of the PowerMe study is to examine the efficacy of the blended CBT on reducing fatigue severity in children with MD. The weekly measurements will be analysed with (1) visual analysis, (2) randomization tests and (3) multilevel modelling.
Visual analysis will be used for an initial assessment of the intervention effects on fatigue severity by examining six features of graphed SCE data: level, variability, trend, immediacy of effect, overlap and consistency of data patterns [52]. On a group level, heterogeneity between individual trajectories will be explored and described.Randomization tests will be used to test if there is a statistical significant effect of CBT on fatigue. These tests have the ability to detect smaller changes than visual analysis alone and test statistical significance. We expect the fatigue severity to be lower in the treatment phase than in the baseline phase. Therefore, we will use a one-tailed alternative hypothesis, measuring the difference in fatigue severity between phases A and B [34, 51].Multilevel modelling will be used to investigate statistical significance and treatment effects using a multiple, single case multilevel modelling strategy based on the modelling suggestions by Moeyaert et al. (2014). This approach can identify case-specific treatment effects and estimated differences between cases. The fluctuations of the weekly and/or aggregated scores between the phases (baseline, intervention and follow-up) are evaluated. More specifically, the analysis focuses on the differences in the intercept and slopes of the weekly scores from one phase to the other. This method has also been validated in small sample sizes (with *N* of 4–8) [53].

All other outcomes will be mapped descriptively. The software program RadQuest will be used to administer questionnaires, which will prevent missing data within questionnaires. According to the study design, missing measurement moments will be handled as missing data and will not be imputated. Analyses of the data will follow the intention-to-treat principle, using the SCDA plug-in package for R software [35, 54].

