**Fig. 1 Fig1:**
[figure not shown]
Proposed explanatory model of contributing factors to MD-related fatigue and targets of the PowerMe intervention

PowerMe is a combination of face-to-face CBT and an online environment to support therapeutic contact and assignments. Using a mostly online approach will limit travelling for the patients. As a result, patients can more optimally use their time and energy on the intervention [13, 23]. The PowerMe intervention is tailored to the individual patient. Each patient will work on personally relevant goals. In addition, the intervention takes into account the age-related differences in children and adolescents, the diverse clinical phenotype of MD that may cause a variety of consequences in daily life and the presence of (one or more) generic factors contributing to fatigue. All generic factors presented in Fig. 1 can be targeted in the intervention. In addition, parents will be included as an at-home coach to improve the effectiveness of the intervention [25, 26].

Although CBTs are traditionally tested using randomized controlled trials, this study design is not applicable when large groups are difficult or impossible to obtain. A study design focusing on the individual level can also be valuable. Both types of study designs provide important, useful and unique information about the effectiveness of an intervention [27]. To investigate the effect of a tailored intervention in patients with a rare disease, a within-subject design is more feasible. A multiple baseline single case experimental design is suitable, because each participant will act as his or her own control comparing data of the baseline phase with the intervention phase [27–29].

We will investigate the efficacy of the PowerMe intervention in a multiple baseline single case experiment. We hypothesize that the intervention significantly reduces perceived fatigue in severely fatigued children and adolescents with MD. Furthermore, it is hypothesized that due to the character of the intervention, a delayed effect will take place, approximately on the half-way point of the individual treatment (in most cases after 8 weeks). In addition, the efficacy of the PowerMe intervention on reducing the negative impact on daily life will be studied by measuring quality of life, school presence and physical functioning.

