### Procedure

To ensure sufficient data points are present to analyse the data, this multiple baseline single case experiment consists of 33 weekly measures of fatigue dispersed over three consecutive phases: baseline, treatment and follow-up. The intervention will be introduced staggered across time. In other words, each participant will start after a different length of the baseline period. The participants are allocated to an intervention start point at random. The following five start points will be randomized: the therapy will start following a baseline period of 5, 6, 7, 8 or 9 weeks. This approach is similar in both groups. The baseline period should be stable. Five to nine data points should give a clear indication of the stability of the baseline [28, 30]. However, extending the baseline period when an unstable baseline is present will cancel out the randomization. For a more rigorous method of testing the effect of the intervention, baseline randomization will be applied. Therefore, baseline stability will not be checked before starting the intervention.

The researcher will contact the patient after randomization has allocated a baseline period between 5 and 9 weeks. At the start of the study, a participant number will be assigned to the patient to ensure confidentiality of personal identifiable patient data throughout the entire study. Participants and their parents receive a link to the online questionnaires each week for 33 weeks: the children fill out assessments about their fatigue and parents report on the school presence of their child. At the start of the study, the patient and parents are asked to fill out additional online questionnaires for the baseline assessment (T0).

After 5–9 weeks, the patient will start with the PowerMe treatment. The guideline for the treatment duration is 16 weeks. However, it can range from 12 to 20 weeks, tailored to the needs of each participant. Afterwards, the patient fills out the (online) post-intervention questionnaires (T1) and continues with the weekly questionnaire for 8–12 weeks. In Fig. 2, an overview of the study design is shown.

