**Fig. 2 Fig2:**
[figure not shown]
Guideline of the multiple baseline design used in the study. Note: Phase B can range from 12 to 20 weeks. Phase A′ is adapted to phase B to reach a total of 33 weekly measurements

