### Power

The sample size and series length are based on literature of randomization tests in multiple baseline single case experiments. Power of a multiple baseline single case experiment is related to the series length [31, 33, 34]. A series length of 30 has a power over 0.8 when the effect size is 1.0 and no autocorrelation is present [33], though some autocorrelation can be expected and will be taken into account. Sample size is based on the primary outcome of fatigue severity using at least 30 weekly measurements. When using randomization tests, a sample size of at least 4 participants per group is necessary to have sufficient statistical power in the randomization test [33, 51]. Based on the literature, the current design of five patients and 33 measurements will be sufficient to reach a statistical significance *p* < .01 using the Wampold-Worsham procedure [33], with significance reached at *p* < .05.

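### The randomization test contrasts phases A and B from the first treatment week, so under the hypothesised delay of about 8 weeks its power is about 0.05 at any effect size

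*Protocol article*

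**What the plan says.** The last paragraph of the Background hypothesises that "a delayed effect will take place, approximately on the half-way point of the individual treatment (in most cases after 8 weeks". The randomization test, under Intended statistical analyses, is defined differently: "We expect the fatigue severity to be lower in the treatment phase than in the baseline phase", and then "we will use a one-tailed alternative hypothesis, measuring the difference in fatigue severity between phases A and B". No lag or transition period is mentioned.

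The design facts that matter are under Procedure and in the Fig. 2 note:

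- Start points: "the therapy will start following a baseline period of 5, 6, 7, 8 or 9 weeks".
- Length of phase B: "The guideline for the treatment duration is 16 weeks"; the Fig. 2 note adds that "Phase B can range from 12 to 20 weeks".
- Series: the experiment "consists of 33 weekly measures of fatigue dispersed over three consecutive phases: baseline, treatment and follow-up".

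The Power section names the Wampold-Worsham procedure with five patients, "with significance reached at *p* < .05", and cites from the literature a power over 0.8 at effect size 1.0 without autocorrelation. It does not mention delay. The Discussion accepts that single case designs often presume an immediate effect and that a delayed one is harder to study, but it does not change the test.

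**The concern.** A randomization test has power only if the true assignment of start points gives a more extreme statistic than the rearranged assignments. That requires the wrong assignments to put affected weeks into phase A, or unaffected weeks into phase B, more often than the true one does. With a stagger of at most 4 weeks and a delay of about 8, no assignment can put an affected week into phase A. Affected and unaffected weeks are then mixed in phase B to much the same degree under every assignment.

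At stake is the analysis on which sample size and series length were based, and the only one that takes its p-value directly from the randomised start points. If the therapy works as hypothesised, this test would reject about as often as under the null. A reader who relies on the cited power could take a non-significant result as evidence against the therapy.

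**Working it through.** **Inputs.** Five patients per test, one at each baseline of 5, 6, 7, 8 and 9 weeks; 33 weekly scores; phase B of 16 weeks (guideline) or, as a variant, to week 33; one-tailed alpha 0.05; onset 8 weeks after start. Assumptions added here: normal errors, lag-1 autocorrelation 0 or 0.3, and effect size d in within-phase SD units. The statistic is the sum over patients of mean(A) − mean(B), referred to all 5! = 120 assignments.

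**The plan's own figures first.** The smallest attainable p is 1/120 = 0.0083, so the statement under Power that p < .01 can be reached is reproduced. The cited power over 0.8 is not reproduced with these start points: an immediate effect of d = 1 gives 0.49 (0.42 with autocorrelation 0.3; 0.76 with both groups of five pooled). The stagger in the cited literature is not given, so that gap is a separate matter. The value 0.49 serves here as the comparator.

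**Why delay removes the power.** Let s be a patient's true baseline length and k the length assigned in a rearrangement.

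- The earliest affected week in any patient is 5 + 8 + 1 = 14. The longest possible baseline ends at week 9. So mean(A) never contains an affected week. The same holds from a delay of 4 weeks upward: 5 + 4 + 1 = 10 > 9.
- With a 16-week B, the rearranged phase B covers weeks k + 1 to k + 16, and the effect is present from week s + 9. Affected weeks in B = (k + 16) − (s + 9) + 1 = k − s + 8.
- Over five patients the k values are the s values reordered, so Σ(k − s) = 0 and the total is 5 × 8 = 40 of 5 × 16 = 80 weeks.
- The noise-free statistic is therefore 40/80 = 0.5d per patient under all 120 assignments. A larger d raises all of them equally.
- With B to week 33, the true assignment gives the smallest noise-free value: 0.6914d, against a maximum of 0.6973d.

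**Simulated power of the unlagged test** (4,000 trials per cell, B = 16 weeks, no autocorrelation):

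| Effect shape | d = 1 | d = 2 | d = 3 |
|---|---|---|---|
| Immediate | 0.49 | 0.92 | 1.00 |
| Step after 1 week | 0.14 | 0.23 | 0.30 |
| Step after 2 weeks | 0.08 | 0.09 | 0.09 |
| Step after 4 weeks | 0.05 | 0.06 | 0.05 |
| Step after 8 weeks | 0.05 | 0.04 | 0.05 |
| Linear build-up over weeks 0–8 | 0.09 | 0.15 | 0.23 |

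Across both lengths of B and both autocorrelations, the 8-week step gives 0.04 to 0.05. With both groups pooled it stays at 0.05. The gradual build-up at d = 1 gives 0.07 to 0.09.

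**A statistic lagged by 8 weeks** (mean of scores up to start + 8 weeks, minus mean from there to week 33; d = 1, no autocorrelation):

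| True onset | Power |
|---|---|
| 8 weeks in every patient | 0.54 (0.47 with autocorrelation 0.3) |
| 7 or 9 weeks | about 0.13 |
| 6 or 10 weeks | about 0.06 |
| Varying over 6–10 weeks between patients | about 0.14 |
| Immediate | about 0.04 |
| Gradual, over 8 or 16 weeks | about 0.05 to 0.07 |

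Its type I error is 0.05.

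**The case against.** The strongest reply is that the randomization test is one of three analyses of the weekly scores. The multilevel model compares intercepts and slopes across baseline, treatment and follow-up, is itself meant to assess significance, and can register a delayed change. This stands. A reader might infer that the trial is almost certain to report no effect whether or not the therapy works. The documents do not support that: the statement is limited to the randomization test under delayed onset, and nothing makes that test the sole decision rule.

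A reader might also infer that visual analysis would penalise a late effect, because immediacy is among its features. It is one of six, and nothing says that its absence counts against the intervention.

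The size of the loss depends on the shape of the effect. A sharp step is an assumption; gradual change is equally compatible with the Discussion's remark that a psychological intervention needs time to work. This too stands, but it raises power only to 0.07–0.09 at d = 1 for a build-up over 8 weeks.

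It is tempting to think that a lagged statistic repairs the test. It does so only if the lag is right. Treatment of 12 to 20 weeks puts the half-way point at weeks 6 to 10, where the lagged power is about 0.14. The narrow stagger is a design limit that analysis code cannot remove.

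Finally, the Discussion warns about delayed effects and about power. That power caution concerns effect size, and even d = 3 leaves power at 0.05. A separate analysis plan might add a lag, but the article does state the contrast, and as stated it does not match the hypothesis.

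**Conclusion.** The concern holds for the randomization test. Under the hypothesised onset at about 8 weeks, the stated A–B contrast has power of about 0.05 whatever the effect size, against 0.49 for an immediate effect of d = 1. The cited power over 0.8 cannot be claimed for the delayed effect.

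The result rests on one patient per start point, a phase B of 16 weeks or running to week 33, and no effect before the delay has passed. It does not depend on exactly 8 weeks: a delay of 4 weeks or more already brings power down to alpha. A non-significant randomization test should not be read as evidence of no effect. No conclusion follows about the power of the multilevel model, which was not examined here.

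**What to change.** Before any outcome data are examined:

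1. Pre-specify a randomization statistic with a fixed 8-week lag: mean fatigue severity up to start + 8 weeks against the mean from there to week 33. Apply the same lag to every permuted start point, which keeps the test exact. Use a fixed lag rather than each patient's own half-way point, because treatment length is tailored after the start.
2. Report the unlagged A–B statistic alongside it, named as such, since the lagged one has almost no power for an immediate effect.
3. State under Power and in the Discussion that the unlagged test has essentially no power for a delayed effect. State also that, at d = 1, the lagged test has power of about 0.54 only if onset is at 8 weeks in every patient, about 0.14 if onset varies over 6 to 10 weeks, and about 0.05 if the effect is immediate or gradual.
4. State that a non-significant randomization test is not evidence of no effect, and that the multilevel model is the planned analysis better able to show a delayed change.

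The cost is some wording and a few lines of code, with no new data. The drawback is dependence on the chosen lag, so it must be fixed in advance and not chosen after looking at the series.

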## Discussion

This paper outlines the study protocol for a multiple baseline single case experiment to investigate the efficacy of a blended CBT on reducing perceived fatigue and the negative impact of fatigue on daily life in children with MD. Fatigue is highly prevalent in children with MD and rated as one of the most burdensome complaints [15]. Other studies show that CBT can effectively reduce fatigue in patients with chronic disease [21, 22]. However, few evidence-based interventions exist for children with fatigue due to a chronic disease [9, 55]. Furthermore, no studies have been found targeting fatigue with a CBT intervention in patients with MD.

The blended care approach of the PowerMe intervention could be a promising working method within specialized care of rare diseases to reach patients country-wide. Travelling is limited, increasing time and energy spend on the intervention and reducing school absence. The tailored approach ensures patients work on individually relevant goals with a personalized treatment plan. Possible fatigue maintaining factors are addressed throughout the intervention. The effect of this individualized intervention will then be measured for each participant using a single case experiment.

The study design has several strengths and limitations. A single case experiment is used to measure the efficacy of an intervention in small groups. It is especially useful in rare diseases like MD, when large sample sizes are not feasible. Moreover, a single case experiment measures the effect of the intervention on an individual level. This corresponds well when investigating the individually tailored PowerMe intervention in a heterogeneous group of MD patients. Thirdly, fatigue will be measured weekly over a course of 33 weeks. The course of fatigue will be measured over time instead of measuring the difference between two data points (before and after treatment). Though this provides valuable information about the course of fatigue over time, the participant needs to commit to the study for a relatively long time. Furthermore, by focusing on perceived fatigue as primary outcome, measured with a validated self-report questionnaire, the risk of response shift bias increases. Though this is the most optimal and accurate way of measuring perceived fatigue, we need to be aware of such a bias when reporting the results of our study. Some difficulties are inherent to this design. Randomization and stable baselines are both important to improve validity. Unfortunately, controlling for a stable baseline within a randomized multiple baseline design is not possible. In addition, a single case design often presumes an immediate effect when a treatment is started. However, a psychological intervention needs time to change unhelpful thoughts and behaviours before an effect can be measured. A delayed effect can be investigated with single case designs, although it is not as straightforward as immediate effects. Regarding the statistical analyses, caution is warranted regarding the power calculation of the randomization test. A large effect size is needed to have sufficient power for this analysis, which may not be a realistic effect size for this type of intervention and outcome. However, large effect sizes have been reported in studies focusing on CBT treatments and literature suggests larger effect sizes are likely in single case designs that focus on established interventions [56, 57]. The PowerMe intervention implements widely used psychological techniques, tailored to children and adolescents with MD. We have also added multilevel modelling as an additional statistical analysis, which can be used in small groups and are more likely to detect changes when smaller effect sizes are present. Lastly, to control for effects of time and other possible confounders, it is recommended to use a concurrent design [28, 29]. However, patients may not be able to start at the same time and therapists may have limited time to treat several patients at the same time. If a concurrent design is not feasible, a non-concurrent design will be used in one or both groups to investigate the effectiveness of the intervention.

In conclusion, fatigue is highly prevalent in children with MD, a rare disease with a highly heterogeneous course and expression. Evidence-based interventions are needed to reduce fatigue and improve quality of life. This study aims to investigate the efficacy of a blended CBT to reduce perceived fatigue in children with MD using a single case experimental design. If the PowerMe intervention shows to be effective and feasible in this study, it could be a valuable addition in clinical practice to treat fatigue in children with MD. However, more research is needed to be able to provide sufficient evidence about the effectiveness of the PowerMe intervention on experienced fatigue [28]. If proven effective, the intervention will be part of an interdisciplinary treatment for patients with MD. Patients with MD often receive many different health care interventions to treat their symptoms. Future research should explore the effectiveness of a combination of treatments, for example, physiotherapy and psychological interventions, to treat fatigue on a mental and physical level.

## Trial status

Recruitment of the PowerMe study is ongoing. The recruitment started in Febuary 2019 and is expected to end in Febuary 2021.

## Data Availability

Data will be made available upon reasonable request.

## Abbreviations

CBT: Cognitive behaviour therapy
CDI: Children’s Depression Inventory
CHQ: Child Health Questionnaire
CIS: Checklist Individual Strength
ICQ: Illness Cognitions Questionnaire
IMP: International Mito Patients
MD: Mitochondrial disease
PedsQL-MFS: Pediatric Quality of Life Inventory Multidimensional Fatigue Scale
SCARED: Screen for Child Anxiety Related Disorders
SCDA: Single-Case Data Analysis
